### 7.3. Outcome Research Assessment

Economic impact will be assessed from the health system and provider perspective, as measured by in-hospital and out-of-hospital healthcare utilization consumed by the newborn/infant and the mother due to low birth weight, infections and health complications. Healthcare resource utilization assessments will be done at delivery (within 2 days for home delivery) and on Day 28 post delivery.

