| General Physical Exam of Neonatev                                     |                                 |                    |                    |                                 |                    |                    |                                 |                    |                    |                          | X                        | X                                 |                                          |
| Outcome Research/Resource Utilization Questions                                  |                                 |                    |                    |                                 |                    |                    |                                 |                    |                    |                          | X                        | X                                 |                                          |

- Each subject will receive 3 IPTp treatment courses of AZCQ or SP during antenatal care (ANC) visits at 4 - 8 week intervals. The first treatment course will be administered during the second trimester (14-26 weeks of gestation as confirmed by ultrasound). The last treatment course should be given to subjects prior to or during 36 weeks of gestation.
- The day of visit for the specified treatment course.
- All tasks should be performed prior to the first dose except AE assessment and bed net distribution.
- Every attempt should be made to follow up the subject at delivery. In the case of home delivery, the subject should report delivery within 24 hours of delivery. Fieldworker should visit the subject at home thereafter within 2-days of subject reporting delivery.
- Day 28 post delivery: window Day 28- Day 42 post delivery.
- Only for a limited number of subjects who participate in macrolide and penicillin resistance test for *Strep. Pneumoniae*. Window: 1 week from 6 months post last IPTp course.

- g. Complete physical exam: general appearance, throat, neck, thyroid, musculoskeletal, skin, lymph nodes, extremities, pulses, pulmonary, cardiac, abdominal, and neurological examination.
- h. Limited physical exam: general appearance, brief pulmonary, cardiac, abdominal and neurological examination.
- i. Ultrasound will be performed only if the urine pregnancy test is positive.
- j. If not done at any prior ANC visit for this pregnancy.

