### **Outcome Research Endpoints**

To assess health economic impact from the health system and provider perspective, as measured by in-hospital and out-of-hospital healthcare utilization for the newborn/infant and the mother consumed due to low birth weight, infections and health complications. The endpoints will include:

1. Number of times a newborn/infant is taken to a local health clinic/physician's office/outpatient hospital clinic including Emergency Room (without having to be admitted) during the first 28 days (window Day 28 - Day 42) of life to attend to a health complication and the primary reason for visit;
2. Number of times a newborn/infant is admitted to a hospital during the first 28 days (window Day 28 - Day 42) of life, including length of hospital stay;
3. Number of times a mother is taken to a local health clinic/physician's office/outpatient hospital clinic including Emergency Room (without having to be admitted) from the time of the administration of the first dose of IPTp through Visit 6 on Day 28 (window Day 28 - Day 42) post delivery for treatment (or follow up) of Anemia, Malaria, STD or other complications and primary reason for the visit;
4. Number of times a mother is admitted to a hospital from the time of the administration of the first dose of IPTp through Visit 6 on Day 28 (window Day 28 - Day 42) post delivery, including length of stay in hospital.

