### 3. STUDY DESIGN

This is a Phase 3, open label, randomized, parallel group study that will compare the efficacy of IPTp regimens of AZCQ and SP in asymptomatic pregnant subjects enrolled during second trimester of pregnancy. Approximately half of the subjects will be primigravidae and secundigravidae pregnant women since they have a higher risk for suboptimal pregnancy outcomes due to malaria. They will be randomized to receive either AZCQ or SP after informed consent is obtained (and assent if applicable) and inclusion/exclusion criteria are determined to have been met. Each subject will receive three IPTp courses of AZCQ or SP during ANC visits at 4 - 8 week intervals. The first treatment course will be administered during the second trimester (14-26 weeks of gestation as confirmed by ultrasound). The last treatment course should be given to subjects prior to or during 36 weeks of gestation. Subjects should be followed up at delivery or within 2 days of subject reporting home delivery (report within 24 hours of delivery), and on Day 28 (window: Day 28 to Day 42) post-delivery. Long lasting insecticidal-treated bednets (LLINs) will be given to all subjects on Day 0 of the study with the instructions to use them; the installation of LLINs will be verified during the first home visits of Treatment Course 1 by fieldworker(s).

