##### For neonates:

- Birth weight of the neonate;
- General physical exam of the neonate;
- Lab diagnosis of ophthalmia neonatorum: collection of conjunctival exudates from neonates with purulent discharge for the lab test before the presumptive treatment is given. The standard empiric regimen of ophthalmia neonatorum presumptive treatment will be given to all neonates at birth per local treatment guidelines;
- AE assessments;
- Outcome research/resource utilization question.

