#### **6.1.6. Visit 6: Follow-up Visit on Day 28 Post Delivery (Window: Day 28 to Day 42)**

The subject will have the following procedures performed at this visit at ANC:

- Concomitant treatment history;
- Limited physical examination;
- Vital signs;
- Hemoglobin level (with HemoCueTM);
- A nasopharyngeal swab for macrolide resistant and penicillin resistant *Streptococcus pneumoniae* from subjects who were tested at baseline;
- AE assessments;

- General physical exam of neonate;
- Outcome research/resource utilization data collection.

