## 7.2. Efficacy Assessments

- Adverse pregnancy outcomes: defined as live-borne neonate (singleton) with LBW (<2,500g), premature births (<37 weeks), abortion (≤28 weeks), still birth (>28 weeks), lost to follow-up prior to termination of pregnancy or delivery, or missing birth weight of the neonates. Following are some details:
  - LBW: defines as birth weight less than 2500 g (up to and including 2499g);
  - Abortion: defines as a pregnancy loss before 28 completed weeks of gestation (≤28 weeks);

- Stillbirth: birth of a baby showing no signs of life. It defines as a pregnancy loss after 28 weeks of gestation (>28 weeks);
- Premature births: the neonate born prior to 37 weeks of gestation (<37 weeks);
- Lost to follow-up prior to termination of pregnancy or delivery.

The sites are asked to make every attempt to follow up subjects through Day 28 post delivery unless the consent is withdrawn.

- Neonate outcomes at birth: birth weight, length, APGAR scores (1/5 minutes), Ballard scores, congenital abnormalities, perinatal and neonatal deaths, ophthalmia neonatorum (lab diagnosis):
  - Birth weight: The weight of a neonate determined immediately after delivery or as soon as feasible thereafter. If home delivery, the subject should contact the study site as soon as possible when the delivery occurs. Field workers will visit home as early as possible within 2 days of subject reporting delivery. Digital weight scale will be used for accurate readings;
  - Ophthalmia neonatorum: laboratory diagnosis will be performed among neonates with purulent discharge. A sample of conjunctival exudates will be taken on a sterile cotton swab before the treatment is given. The collected sample will be sent to a central lab to test *N. gonorrhoeae* and *C. trachomatis* using PCR assay (Amplicor CT/NG, Roche). The standard presumptive treatment/prophylaxis for ophthalmia neonatorum will be given to neonates at birth per local treatment guidelines;
- Hemoglobin levels: HemoCueTM, via finger stick or peripheral blood collection;
- Diagnosis of pre-eclampsia from Week 20 to delivery:
  - (1) Systolic blood pressure of at least 140 mmHg and/or diastolic blood pressure of at least 90 mmHg, measured on two separate readings taken at least 4 hours apart, AND
  - (2) Proteinuria at least 300 mg protein in a 24 hour urine collection.

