### 9.3. Outcome Research Analysis

Health economic outcomes will be assessed in terms of the health care resource utilization consumed by newborns/infants and mothers due to low birth weight, anemia, sexually transmitted diseases or sub-optimal pregnancy outcome. Measures of resource utilization will include in-hospital and out-of-hospital services for newborn/infant and mother, and associated care.

In-hospital services will include number of times of hospitalization, length of hospital stay and the numbers and durations of related admissions/re-admissions. Out-of-hospital services will include local health clinic/physician's office/outpatient hospital clinic including emergency room (without having to be admitted) to attend to a health complication(s). Data will be summarized descriptively by treatment group.

Analysis of health economics outcomes will include an analysis of the number of hospitalization times and durations of hospital stays as well as number of outpatient hospital visits. Statistical methods will include the Wilcoxon or t-test for durations of total hospital stays and number of outpatient hospital visits. Descriptive statistics will be used in summarizing the results of the individual items in the healthcare resource utilization questionnaire. Cost analysis of these items may be performed separately, outside the scope of the current analysis plan.

Contributing to the health economic impact endpoint is the physician/subject questionnaire.

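### Maternal health-care use is counted from the first dose but first asked about at delivery or Day 28, and no question is tied to a pregnancy loss

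*Protocol*

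**What the plan says.** Section 2.2 (Outcome Research Endpoints) and the protocol summary define two maternal counts. Endpoint 3 is outpatient attendance, including the emergency room without admission. Endpoint 4 is hospital admission. Both run "from the time of the administration of the first dose of IPTp through Visit 6 on Day 28" (window to Day 42). Section 2.2 also asks for the primary reason for each outpatient visit and the length of each stay.

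Collection is placed as follows.

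- **Section 7.3:** "Healthcare resource utilization assessments will be done at delivery (within 2 days for home delivery) and on Day 28 post delivery". The section covers use by the mother as well as the infant.
- **Schedule of Activities:** the row "Outcome Research/Resource Utilization Questions" is marked at Visits 5 and 6 and is blank at Visits 1 to 4.
- **Sections 6.1.2 to 6.1.4 (Visits 2, 3 and 4):** no resource-use item.
- **Sections 6.1.5.1 and 6.1.5.2 (Visit 5, hospital and home delivery):** "Outcome research/resource utilization question" appears in the list for neonates and not in the list for mothers.
- **Section 6.1.6 (Visit 6):** "Outcome research/resource utilization data collection".

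Section 9.3 names a physician/subject questionnaire as the instrument. It includes care due to sub-optimal pregnancy outcome in what is to be measured, and it plans a comparison: "Statistical methods will include the Wilcoxon or t-test for durations of total hospital stays and number of outpatient hospital visits".

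**The concern.** The counting period begins in the second trimester, but the first scheduled question comes at or after birth, although the woman attends three visits in between. Outpatient attendances away from the study site are the kind of event most easily forgotten over such a period. Under-counting pulls a true difference between arms towards zero, and because the trial is open label, reporting could also differ by arm.

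The second problem is who gets asked. The collection times are defined by delivery. Abortion is one component of the sub-optimal outcome, and Section 9.3 wants to measure the care that such outcomes cause. Women whose pregnancies end early are the ones for whom the plan gives no clear time of asking. Later analysis cannot recover data that were never collected.

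**Working it through.** The protocol states no recall length, so there is no figure to reproduce. The length follows from the visit timing.

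**Inputs**

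- First dose at gestational week 14 to 26 (Section 3: "The first treatment course will be administered during the second trimester (14-26 weeks of gestation as confirmed by ultrasound").
- Lower limit of term: 37 weeks (Section 7.2: "Premature births: the neonate born prior to 37 weeks of gestation (<37 weeks").
- Upper value for term birth: 40 weeks. This is an assumption; the protocol does not state it.
- Visit 6: Day 28 to Day 42 after delivery, that is, 4 to 6 weeks.

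**Formulas**

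- Shortest interval to Visit 5 = week of delivery − 26; longest = week of delivery − 14.
- Shortest interval to Visit 6 = week of delivery + 4 − 26; longest = week of delivery + 6 − 14.

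| Week of delivery | First dose to Visit 5 (weeks) | First dose to Visit 6 (weeks) |
|---|---|---|
| 29 | 3 to 15 | 7 to 21 |
| 34 | 8 to 20 | 12 to 26 |
| 37 | 11 to 23 | 15 to 29 |
| 40 | 14 to 26 | 18 to 32 |

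For births at 37 to 40 weeks, the first question at Visit 5 therefore comes 37 − 26 = 11 to 40 − 14 = 26 weeks after the first dose. If the Visit 5 lists are followed literally and the mother is first asked at Visit 6, the range is 37 + 4 − 26 = 15 to 40 + 6 − 14 = 32 weeks.

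**What asking at Visits 2 to 4 would do.** Courses are 4 to 8 weeks apart, so the intervals to Visits 2 and 3 become 4 to 8 weeks. A woman entered at week 14 has Visit 3 at week 14 + 8 = 22 to 14 + 16 = 30 and Visit 4 at week 36 to 38. Her interval from Visit 3 to Visit 4 is then 36 − 30 = 6 to 38 − 22 = 16 weeks. From Visit 4 to a birth at week 40 is 2 to 4 weeks. The longest single interval for the earliest entrant thus falls from 26 weeks to at most 16.

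**Pregnancies that end early**

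- *Induced abortion:* Section 8.9 ends follow-up at termination, and no resource-use question is placed there.
- *Spontaneous abortion:* Section 6.2 keeps women in follow-up to Day 28 after delivery unless they withdraw consent or move away. The protocol does not say whether the delivery and Day 28 visits apply after an abortion.
- *Lost before delivery:* neither Visit 5 nor Visit 6 takes place, so nothing is collected by these questions, even for women who attended Visits 2 to 4.

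The protocol gives no rate for abortion or loss to follow-up, so the number of women affected cannot be computed.

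**The case against.** The best defence is that the counts need not rest on memory. The instrument involves the physician, and Section 11.1 says that source documents are usually hospital or physician charts. Adverse events and medications are recorded at every study visit, Section 6.1.8 asks women with any illness to report to the study physician at once, and Section 7.2 records malaria, STI and bacterial infection diagnoses whenever they occur. An adverse event that leads to admission is an SAE, to be notified within 24 hours of awareness (Sections 8.5 and 8.12.1).

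This stands in part for admissions, so endpoint 4 is less exposed. It does not settle endpoint 3. Section 8.6 excludes routine emergency room admissions from hospitalization, adverse event and medication pages do not count attendances, and no text says that any of these records feed the outcome research counts.

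A second defence is that the neonate heading at Visit 5 is only list placement, since Section 7.3 and the schedule row cover the mother too. That is a fair reading, and the 11 to 26 week range assumes it. The lists still permit the other reading.

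Two stronger readings are tempting. A reader might infer that any woman without a delivery visit has missing data. The documents do not support this: Visit 6 collects the same information, so a missed Visit 5 alone loses nothing. A reader might also infer a large sample-size penalty, nearly threefold if 40% of visits were forgotten and the spread stayed the same, since 1/0.6² = 2.8. The protocol gives neither a forgetting rate nor a target difference for these endpoints, and the spread would not stay the same. For Poisson counts thinned at random, variance falls with the mean and the factor is 0.6/0.36 = 1.7. Neither multiplier should be attached to this plan.

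It is also fair to say that asking more often does not remove arm-related reporting in an open-label trial.

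**Conclusion.** The point holds as a mismatch between the period counted and the times of asking. It mainly affects endpoint 3 and, to a lesser extent, endpoint 4. For births at 37 to 40 weeks the first question comes 11 to 26 weeks after the first dose, or 15 to 32 weeks if the mother is first asked at Visit 6. Both ranges rest on the 40-week assumption and are shorter for preterm births. That the answers depend largely on recall is an inference from the schedule; the protocol does not say so.

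The gap in coverage is definite for induced abortion and for loss before delivery, and undefined for spontaneous abortion. The size of any resulting bias cannot be derived from the document.

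These are outcome research endpoints, largely descriptive, with tests named for length of stay and outpatient visits. No primary or secondary efficacy conclusion depends on them. The point is a minor, inexpensive improvement.

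**What to change.** 1. Add a maternal resource-use question covering the time since the last visit to Sections 6.1.2, 6.1.3 and 6.1.4 (Visits 2, 3 and 4), and mark those visits in the Schedule of Activities.
2. List the item under mothers at Visit 5 in both Sections 6.1.5.1 and 6.1.5.2, keeping the neonatal item where it is.
3. Ask it at the contact that records a pregnancy loss, whether induced or spontaneous, and state whether the delivery and Day 28 visits apply after an abortion.
4. Amend Section 7.3 to match, and define endpoints 3 and 4 as the sum over intervals, so that a woman lost before delivery still contributes what was recorded up to her last visit.

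The cost is a few more CRF items at visits already scheduled, with no new visit. The remaining limits are an interval of up to 16 weeks between Visits 3 and 4 for the earliest entrants and the possibility of arm-related reporting.

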## 8. ADVERSE EVENT REPORTING

### 8.1. Adverse Events

All observed or volunteered adverse events regardless of treatment group or suspected causal relationship to the investigational product(s) will be reported as described in the following sections.

For all adverse events, the investigator must pursue and obtain information adequate both to determine the outcome of the adverse event and to assess whether it meets the criteria for classification as a serious adverse event requiring immediate notification to Pfizer or its designated representative. For all adverse events, sufficient information should be obtained by the investigator to determine the causality of the adverse event. The investigator is required to assess causality. For adverse events with a causal relationship to the investigational product, follow-up by the investigator is required until the event or its sequelae resolve or stabilize at a level acceptable to the investigator, and Pfizer concurs with that assessment.

### 8.2. Reporting Period

For serious adverse events, the reporting period to Pfizer or its designated representative begins from the time that the subject provides informed consent, which is obtained prior to the subject's participation in the study, ie, prior to undergoing any study-related procedure and/or receiving investigational product, **through Day 42 and including 39 calendar days after the last administration of the investigational product or until the last study visit (which ever is later)**. Any serious adverse event occurring any time after the reporting period must be promptly reported if a causal relationship to investigational product is suspected.

Adverse events (serious and non-serious) should be recorded on the CRF from the time the subject has taken at least one dose of study treatment through last subject visit.

### 8.3. Definition of an Adverse Event

An adverse event is any untoward medical occurrence in a clinical investigation subject administered a product or medical device; the event need not necessarily have a causal relationship with the treatment or usage. Examples of adverse events include but are not limited to:

- Abnormal test findings;
- Clinically significant symptoms and signs;
- Changes in physical examination findings;
- Hypersensitivity;

- Progression/worsening of underlying disease.

Additionally, they may include the signs or symptoms resulting from:

- Drug overdose;
- Drug withdrawal;
- Drug abuse;
- Drug misuse;
- Drug interactions;
- Drug dependency;
- Extravasation.

#### **8.4. Abnormal Test Findings**

The criteria for determining whether an abnormal objective test finding should be reported as an adverse event are as follows:

- Test result is associated with accompanying symptoms; and/or
- Test result requires additional diagnostic testing or medical/surgical intervention; and/or
- Test result leads to a change in study dosing or discontinuation from the study, significant additional concomitant drug treatment, or other therapy; and/or
- Test result is considered to be an adverse event by the investigator or sponsor.

Merely repeating an abnormal test, in the absence of any of the above conditions, does not constitute an adverse event. Any abnormal test result that is determined to be an error does not require reporting as an adverse event.

#### **8.5. Serious Adverse Events**

A serious adverse event or serious adverse drug reaction is any untoward medical occurrence at any dose **for mothers or fetus** that:

- Results in death;
- Is life-threatening (immediate risk of death);
- Requires inpatient hospitalization or prolongation of existing hospitalization;

- Results in persistent or significant disability/incapacity;
- Results in congenital anomaly/birth defect.

Medical and scientific judgment should be exercised in determining whether an event is an important medical event. An important medical event may not be immediately life-threatening and/or result in death or hospitalization. However, if it is determined that the event may jeopardize the subject and/or may require intervention to prevent one of the other adverse event outcomes, the important medical event should be reported as serious.

Examples of such events are intensive treatment in an emergency room or at home for allergic bronchospasm; blood dyscrasias or convulsions that do not result in hospitalization; or development of drug dependency or drug abuse.

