### **Safety Endpoints**

Safety and tolerability will be assessed by spontaneously reported adverse event reports, vital signs, physical examination, laboratory tests including hemoglobin and urine test for glucose and protein, and adverse pregnancy outcomes for mothers and by the general physical examination for the neonates through Day 28 (window Day 28 to Day 42) post delivery.

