### **8.9. Exposure During Pregnancy**

This is a study exclusively in pregnant women. Enrolled subjects will be asymptomatic pregnant women who will receive study drugs for preventive treatment of malaria. All pregnancy-related AEs and pregnancy outcomes will be recorded on CRF pages as required clinical study data. Since all the information generally included on an Exposure In Utero (EIU) form will be collected on CRF paper, a separate EIU form is not required.

Subjects will be followed up to Day 28 post delivery (window: Day 28 to Day 42) for pregnancy outcomes or until pregnancy termination (ie, induced abortion). The reason(s) for an induced abortion should be specified.

If the outcome of the pregnancy meets the criteria for immediate classification as a serious adverse event (ie, spontaneous abortion, stillbirth, neonatal death, or congenital anomaly [including that in an aborted fetus, stillbirth or neonatal death]), the investigator should follow the procedures for reporting serious adverse events.

In the case of a live birth, the “normality” of the newborn can be assessed at the time of birth, or as soon thereafter as possible, and at Day 28 post delivery (window: Day 28 to Day 42). The “normality” of an aborted fetus can be assessed by gross visual inspection, unless pre-abortion test findings are suggestive of a congenital anomaly.

Additional information about pregnancy outcomes that are classified as serious adverse events follows:

- “Spontaneous abortion” includes miscarriage and missed abortion.
- All neonatal deaths that occur within 1 month of birth should be reported, without regard to causality, as serious adverse events. In addition, any infant death after 1 month that the investigator assesses as possibly related to the Exposure in Utero to the investigational medication should be reported.

Additional information regarding the Exposure in Utero may be requested by the investigator. Further follow-up of birth outcomes will be handled on a case-by-case basis (eg, follow-up on preterm infants to identify developmental delays). In the case of paternal exposure, the investigator must obtain permission from the subject’s partner in order to conduct any follow-up or collect any information.

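### The adverse event and SAE definitions (Sections 8.3 and 8.5) do not name the live-born infant, in conflict with the protocol's own neonatal safety follow-up, and infant deaths between one month and Visit 6 are reportable only if judged possibly related

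*Protocol*

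**What the plan says.** Section 8.3 defines an adverse event as "any untoward medical occurrence in a clinical investigation subject administered a product or medical device". Section 8.5 says that an SAE "is any untoward medical occurrence at any dose for mothers or fetus that" leads to death, a threat to life, hospital admission, disability or a birth defect.

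Section 8.9 adds rules for pregnancy outcomes. It classes "spontaneous abortion, stillbirth, neonatal death, or congenital anomaly" as serious. On deaths after live birth it has two rules. Up to one month: "All neonatal deaths that occur within 1 month of birth should be reported, without regard to causality, as serious adverse events". After that, what is to be reported is "any infant death after 1 month that the investigator assesses as possibly related to the Exposure in Utero".

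Other sections treat the infant as part of safety follow-up. The safety endpoints in Section 2.2 include assessment "by the general physical examination for the neonates through Day 28 (window Day 28 to Day 42) post delivery". Sections 6.1.5.1 and 6.1.5.2 list adverse event assessments for neonates at hospital and home delivery. Section 6.1.6 pairs an adverse event assessment with a neonatal examination at Visit 6. Section 7.1 includes hospital stays and other complications in the neonatal examination. Section 8.1 requires adverse events to be reported whatever the suspected cause, and Section 8.2 runs SAE reporting at least to the last study visit.

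**The concern.** Every infant in the trial is exposed to study drug in utero, and Section 1.5.2.4 states that no well-controlled study has evaluated giving the two drugs together in pregnancy. The SAE definition decides which events carry the 24-hour notification duty in Section 8.12.1. If the definition leaves out the live-born infant while other sections put the infant in scope, two sites can handle the same neonatal admission differently, and both can point to the protocol. Infant SAE counts would then depend partly on how each site reads the text, and prompt notification of the sponsor would not be assured.

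The one-month rule raises a second, smaller question. It makes reporting of some infant deaths within planned follow-up depend on the investigator's opinion about cause, whereas Section 8.1 says that reporting does not depend on suspected cause.

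**Working it through.** The plan gives no figure to reproduce. The check sets the passages side by side and then works out one interval.

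**Whose events count under the definitions.**
- Section 8.3: a subject who was administered a product. The infant is not dosed, and Section 6.1.8 itself mentions subjects and their babies separately.
- Section 8.5: the mother or the fetus. After live birth the child is neither.

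**What Section 8.9 restores for the live-born infant.**
- Congenital anomaly: yes.
- Death within one month: yes, whatever the cause.
- Death after one month: only if judged possibly related.
- Non-fatal life-threatening illness, admission or disability: not mentioned.

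**A test case.** A live-born infant is admitted with sepsis before Visit 6 and recovers.
- On Sections 8.3, 8.5 and 8.9 read literally, this is not an SAE.
- On Sections 6.1.5.1, 6.1.5.2 and 6.1.6, infant events may be recorded as adverse events. Section 8.12 then requires each adverse event to be assessed for seriousness. Section 8.6 treats an adverse event with hospitalization as serious and does not restrict this to mother or fetus.
- Section 8.12.1 applies the 24-hour limit to reports of Exposure in Utero cases as well, which could be read to take in this infant.

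The protocol therefore supports two answers to a routine question. The uncertain period for non-fatal events runs from birth to Visit 6, that is 28 to 42 days.

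**Infant deaths that depend on a causality opinion.** Let *d* be the day of Visit 6 after delivery and *m* the length of one month in days. The interval up to Visit 6 is max(0, *d* − *m*).
- *d* lies between 28 and 42 (the Visit 6 window).
- *m* is taken as 28 to 31. This is an assumption, because the protocol does not state one month in days.
- *d* = 42, *m* = 28: 42 − 28 = 14 days.
- *d* = 42, *m* = 31: 42 − 31 = 11 days.
- *d* = 28, *m* = 28: 28 − 28 = 0 days.
- *d* = 28, *m* = 31: the visit comes before one month has passed, so 0 days.

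The interval is thus 0 to 14 days. Visit 6 is taken as the end point because it is the last scheduled neonatal examination. Visit 7 applies only to the nasopharyngeal swab subset and lists no infant examination.

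**The case against.** The strongest reply is that the infant is well observed and that several routes lead to a report. Neonatal adverse events are assessed at delivery and Visit 6. Section 6.1.8 asks that sick babies be brought to the study physician. Adverse events, serious or not, go on the CRF to the last visit (Section 8.2). Sections 8.6 and 8.12.1 can be read to cover an infant admission. Under Section 8.8 an event of unknown cause is handled as related, which narrows the condition on late deaths. All of this stands. It shows that the fault is an inconsistency and not an absence of data. It does not remove the fault, because each of these routes relies on reading past the definitions in Sections 8.3 and 8.5.

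Three stronger readings are tempting, and the documents do not support them.
- A reader might infer that serious infant events go unreported altogether. Neonatal deaths to one month and congenital anomalies are already SAEs under Section 8.9.
- A reader who sees the resource-use endpoint, "Number of times a newborn/infant is admitted to a hospital during the first 28 days (window Day 28 - Day 42) of life", might infer that infant admissions are collected only for health economics. Section 7.1 lists hospital stays among the safety assessments.
- Because the trial is open label, a reader might infer that late deaths enter the data through a judgment made with the arm known, so that the comparison between arms is biased. Section 8.9 governs what is reported. It does not say that unrelated late deaths are left off the CRF. The safety tables in Section 9.4 draw on collected data, and Section 9.6 does not confine the IDMC to SAEs.

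**Conclusion.** The point holds as a conflict between rules. Sections 8.3 and 8.5 leave it unclear whether a non-fatal serious event in a live-born infant is an SAE, from birth to Visit 6. For deaths the conflict with Section 8.1 is narrower: it concerns only deaths judged unrelated, after one month and before Visit 6, an interval of 0 to about 14 days. That range rests on a month of 28 to 31 days and on Visit 6 as the end of infant follow-up.

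The number of infants concerned cannot be given. The protocol states no expected rate of serious neonatal illness or of death after one month. Neither the planned enrolment nor the share of follow-up days would measure it. The consequence lies in the consistency and speed of safety reporting. The primary endpoint, the alpha level and the sample size are not touched.

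**What to change.** - In Sections 8.3 and 8.5, name the live-born infant, through Visit 6, alongside the mother and fetus.
- In Section 8.9, make every infant death through Visit 6 reportable as an SAE regardless of causality, and keep the relatedness condition only for later deaths. Fixing the limit by visit also removes the undefined length of one month.
- Check that Sections 6.1.5, 6.1.6, 7.1, 8.2, 8.6 and 8.12.1 agree with the revised definitions.
- Reconcile newborn admissions recorded at delivery and Visit 6 against infant SAE reports.

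The cost is an amendment to the protocol text and CRF guideline, and somewhat more SAE reports to process. No new visit or data item is needed.
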